#### 6.4.2 TREATMENT ALLOCATION

Eligible patients in each study group will be allocated to receive study intervention (active treatment or placebo as a comparator) which is defined as follows:

- Active treatment: sequential intravenous administration of NOAC-specific antidote (idarucizumab or andexanet) and rtPA (alteplase) infusion, or
- Comparator treatment: sequential intravenous administration of NOAC-specific antidote placebo (infusion of 0.9% NaCl) and rtPA corresponding placebo (infusion of 0.9% NaCl).

---

#### 6.4.3 RANDOMISATION PROCESS

Randomisation will be performed by the investigator (or trained designee) in the eCRF using the predefined randomisation algorithm built into the eCRF software and is available 24/7 (see [Section 7.3.1](#)).

The investigator will enter specific patient information to allow identification of the participant (date of birth) and confirm that information to perform randomisation is available (listed below).

- All eligibility criteria are met at the time of randomisation
- Patient should be able to start study treatment (i.e., thrombolysis) within 4.5h, but not later than within 6h from AIS onset
- Results of anti-IIa or anti-Xa activity/ blood concentration of dabigatran as per NOAC taken before AIS must be available before randomisation. However, in patients on dabigatran, it is possible to enrol such a subject into the study based solely on a patient's or witness' report on the last intake of the anticoagulant ie, when it was administered within the last 24 hours preceding initiation of the study treatment. In these situations it is obligatory to collect and store blood for post-hoc anti-IIa testing. The procedure is described in the Laboratory Manual.

The AIS NIHSS severity score must be provided to perform randomisation (stratification factor) and unique patient randomisation number will be generated.

Once patient have been randomised, the eCRF system will generate an automatic notification informing the unblinded personnel of the appropriate to prepare allocated study treatment accordingly.

The eCRF completion manual including detailed instructions how to perform randomisation of a patient will be provided to each study site.

#### 6.4.4 POST-RANDOMISATION ACTIONS

After generating patient randomization number in the eCRF by the investigator, unblinded personnel will receive notification about allocated study treatment and will prepare study treatment (active or placebo) based on notification generated via eCRF.

Administration of sequential therapy should be initiated immediately after receiving masked study medications ready for use.

Administration of rtPA (second component of the study intervention) should be initiated within 4.5h time window calculated from the onset of AIS symptoms, but no later than 6h in specific circumstances (i.e. randomisation was performed correctly but unavoidable factors caused delay in administration of rtPA beyond 4.5 hours). Delay of the rtPA bolus administration beyond 6h from the AIS onset is not allowed.

Details of preparing active and placebo treatment will be included in the Pharmacy Manual provided to each study site.

### 6.5 STUDY VISITS AND PROCEDURES OVERVIEW

The STROACT study includes screening period, treatment administration and post-treatment follow-up.

Due to significant time constraints for appropriate standard AIS treatment initiation, or may benefit from participating in the study, informed consent should be obtained as soon as possible (see [Section 6.3](#)).

An absolute condition for carrying out any activities specifically related to the study is the prior obtaining of informed consent from the person enrolled in the study.

#### 6.5.1 VISIT 0 (PRE-TREATMENT) – SCREENING, ENROLMENT AND RANDOMISATION

The following examinations and procedures should be performed in the patient considered for enrolment and randomisation in the study:

1. Medical history with demographic information (obtained from the patient, his family, or the Emergency Medical Team responsible for patient's transfer to the hospital), including:
  - a. concomitant diseases and medications taken; it is important to determine when the last dose of the oral anticoagulant was taken
  - b. functional status prior to the current acute stroke (based on modified Rankin Scale [mRS])
  - c. the exact time of onset of symptoms of the current IS or the time when the patient was last seen without these symptoms
2. Verification of inclusion/ exclusion criteria.
3. ECG.  
**NOTE 1:** ECG must be performed once preferably within the first 24 hours from AIS but not later than 72 hours.
4. Physical examination.
5. Vital signs (BP and HR).
6. Signs and symptoms of infection(s).
7. Neurologic examination based on National Institutes of Health Stroke Scale (NIHSS).
8. Establishment of intravenous access (if not present yet); two are preferred for enrolled patients within groups B and C i.e., those on apixaban and rivaroxaban).

9. Collection of blood sample for the following lab tests:

- a. Anti-IIa activity for dabigatran or anti-Xa for rivaroxaban or apixaban or blood concentration of dabigatran.

NOTE 1: However, in patients on dabigatran, it is possible to enrol such a subject into the study based solely on a patient's or witness' report on the last intake of the anticoagulant ie, when it was administered within the last 24 hours preceding initiation of the study treatment. In these situations it is obligatory to collect and store blood for post-hoc anti-IIa testing. The procedure is described in the Laboratory Manual.

- b. Additional coagulation parameters: INR, APTT, fibrinogen
- c. Complete blood count (CBC) with platelet count
- d. Blood glucose concentration
- e. Biochemistry panel including electrolytes, serum creatinine (eGFR), CRP
- f. Troponin I concentration
- g. Transaminases (AlAT, AspAT) and bilirubin
- h. Albumin
- i. BNP/ NT-proBNP plasma concentration

10. Brain imaging – contrast-free CT scan (whenever possible with an assessment of the severity of early ischemic lesions preferably using the ASPECTS scale) or MRI (minimum requirements are DWI, SWI and FLAIR sequences, or equivalents).

11. DUS of extracranial / intracranial arteries.

NOTE 1: The test should be performed at least once during hospitalization (V0-V3).

12. Echocardiography.

NOTE 1: The test should be performed at least once during hospitalization (V0-V3).

The patient must be closely monitored, and any AEs/ Ars must be recorded in the patient's medical record and in the eCRF.

NOTE 1: If the patient presents with  $\geq 6$  points on the NIHSS scale, or the investigator finds a composition of symptoms suggestive of large vessel occlusion (LVO), it is necessary to expand the neuroimaging with CT or MRI angiography of carotid / vertebral / circle of Willis arteries to assess the indication for primary mechanical thrombectomy.

NOTE 2: If patient's blood pressure is exceeding  $> 185/110$  mmHg, the blood pressure should be lowered by pharmacological means prior to randomisation and/or study treatment administration (e.g., labetalol or urapidil given in boluses and/or continuous infusion using an infusion pump. In the absence of sustained satisfactory response, i.e. inability to achieve blood pressure  $\leq 185/110$  mmHg, or suspected need for aggressive medications use (labetalol, urapidil) to maintain blood pressure below this level during further reversal and thrombolytic treatment, excludes the patient from the study (see exclusion criterion #30).

NOTE 3: The patient should be included in the study and randomized as soon as possible after the onset of stroke symptoms (time of randomisation should not exceed 3.0 h time window), so that thrombolytic treatment (rtPA) or corresponding placebo can be administered within 4.5 hours window from the onset of AIS symptoms (but no later than 6 hours in special circumstances).

NOTE 4: Most of activities / procedures required in the STROACT study protocol are included in the standard of care protocols expected to be carried out in patients admitted to the hospital with preliminary diagnosis of stroke. If any of them have already been performed as part of a routine

clinical evaluation (i.e., not specifically for the purposes of this clinical trial), there is no need to repeat them after obtaining the patient's informed consent.

#### 6.5.2 VISIT 1 (DAY 1) – STUDY TREATMENT ADMINISTRATION

After obtaining lab results of anti-IIa activity for dabigatran (or dabigatran concentration itself) or anti-Xa for rivaroxaban or apixaban confirming high anticoagulation activity (>50 ng/ml) study treatment can be administered. However, in patients on dabigatran, it is possible to enrol such a subject into the study based solely on a patient's or witness' report on the last intake of the anticoagulant ie, when it was administered within the last 24 hours preceding initiation of the study treatment. In these situations it is obligatory to collect and store blood for post-hoc anti-IIa testing. The procedure is described in the Laboratory Manual. Blinded study treatment will be dispensed by unblinded personnel according to the treatment allocation instruction received via eCRF notification (see [Section 6.4.3](#)).

Study treatment will be administered according to the study protocol as a as sequential intravenous administration of NOAC-specific antidote (idarucizumab or andexanet) and tPA (alteplase) or corresponding placebos for each of the study treatment components. **Please refer to dosing instructions in [Section 7.1.2](#).**

1. Vital signs. BP and HR should be monitored and recorded:
  - in the 1. hour
  - in the 2. hour
  - in the 3. hour
  - in the 4. hour
  - in the 5. hour
  - in the 6. hourfrom the start of study treatment administration.
2. Two consecutive blood sample for anti-Xa activity for rivaroxaban or apixaban must be collected:
  - after completion of antidote (or antidote placebo) bolus injection
  - after completion of rtPA (or corresponding placebo) infusion.

Measurements anti-IIa 2nd and 3rd are only facultative.

The start and completion time of each study treatment component, time of blood sample collection for assessment of anti-IIa/Xa activity must be recorded in patient medical records and in eCRF.

3. Review of concomitant medications.
4. DUS of extracranial / intracranial arteries (if not done before).  
NOTE 1: The test should be performed at least once during hospitalization (V0-V3).
5. Echocardiography if not done before).  
NOTE 1: The test should be performed at least once during hospitalization (V0-V3).
6. Collection of blood sample for measure of blood glucose concentration. Obligatory only in cases where the screening value was beyond that defined in inclusion/exclusion criteria.
7. ECG (if not done before).  
NOTE 1: ECG must be performed once preferably within the first 24 hours from AIS but not later than 72 hours.
8. Review of safety endpoints:
  - 1) any symptomatic intracranial haemorrhage (sICH),

- 2) any life threatening extracranial bleeding,
- 3) recurrent or new acute thromboembolic stroke,
- 4) any life threatening thromboembolic complications,
- 5) any significant allergic reactions assumed to be related with the administered substances (antidotes, rtPA).

Patient must be closely monitored during the study treatment administration and any AEs/Ars recorded in patient's medical records and in eCRF.

---

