h – The first blood sample for determination of anti-IIa / anti-Xa activity or dabigatran blood concentration in the respective arm of the study (corresponding to NOAC plasma concentration) should be collected and processed immediately after obtaining ICF; patients with NOAC plasma concentration  $\leq 50$  ng/ml do not qualify for antidote administration and will be treated according to standard of care, which may include thrombolytic treatment. However, in patients on dabigatran, it is possible to enroll such a subject into the study based solely on a patient's or witness' report on the last intake of the anticoagulant ie, when it was administered within the last 24 hours preceding initiation of the study treatment. In these situations, it is obligatory to collect and store blood for post-hoc anti-IIa testing. The procedure is described in the Laboratory Manual.

i – The second blood sample for determination of anti-Xa (corresponding to NOAC plasma concentration) should be taken after NOAC-specific antidote bolus infusion (or corresponding placebo); the third blood sample should be collected after completion of rtPA (or corresponding placebo) administration.

j- Please note that in the STROACT trial we plan to estimate anti-IIa activity only in the pre-treatment stage of the study (a single measurement: either prospective ie, when treatment decisions are based on the blood test result, or retrospective ie, in cases where treatment decisions are based solely on drug administration history). Whereas anti-IIa 2nd (after infusion of NOAC-specific antidote bolus or corresponding placebo) and 3rd measurements (after completion of rtPA or corresponding placebo administration) are only facultative in this arm of the project. The second and third dabigatran blood measurements should not be performed.

k – Brain CT is preferred.

l – Mandatory examination for patients with **NIHSS  $\geq 6$**  or other clinical suspicion of Large Vessel Occlusion (LVO) and qualifying the patient to mechanical thrombectomy (exclusion from STROACT study).

m – Randomisation should be performed within 3.0 hrs from IS symptoms onset to allow timely preparation of the allocated study treatment to be initiated within 4.5 hr (not later than 6.0h) from the IS symptoms onset; **if randomisation time is  $>3.0$  hrs from the onset of IS symptoms investigator should consider patient withdrawal from the study.**

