### 2.3.1 KNOWN POTENTIAL RISKS

Patients with AIS are the population with multiple and various comorbidities, and high total cardiovascular risk.

The most severe complication related to rtPA administration is symptomatic intracerebral haemorrhage (sICH), which occurs in 3-7% of all treated patients, and is associated with poor functional outcome (Hacke W et al, 2008) (Sandercock P et al, 2012) (Karaszewski B et al, 2015) (Yaghi S et al., 2014). Meta-analysis of nine trials of rtPA in ischemic stroke (Whiteley WN et al, 2016) showed increased risk of type 2 parenchymal haemorrhage (PH2), of haemorrhage as per SITS-MOST definition, and fatal intracerebral haemorrhage in IVT group.

In REVERSE-AD trial (A Study of the RE-VERSAl Effects of Idarucizumab on Active Dabigatran), a multicentre, prospective, open-label study, patients with life-threatening or uncontrolled bleeding and patients who required emergency surgery or other urgent procedures, were treated with 5.0 g of intravenous idarucizumab. Median maximum reversal value was 100% in the first 4 hrs. Most patients achieved complete reversal as measured by ECT (82%), or dTT (99%). The adverse reactions reported in ≥5% of patients were constipation and nausea. In 33 (6.56%) patients reported thrombotic

events, and most of these patients were not on antithrombotic therapy at the time of the event (Pollack CV et al, 2017).

In ANNEXA-4 trial (The Andexanet Alfa, a Novel Antidote to the Anticoagulation Effects of Factor Xa Inhibitors), a single-group cohort study, patients with acute major bleeding – 64% intracranial and 26% gastrointestinal – were treated with andexanet alfa in intravenous bolus over 30 minutes, followed by continuous infusion for 120 min. Median anti-FXa activity decreased was 92% for both apixaban and rivaroxaban patients. There were 34 patients (10%) with a thrombotic event during 30-day follow-up period (Connolly SJ et al, 2019).

---

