## 4.2 BLINDING

The STROACT study is designed as double-blind placebo controlled clinical trial; therefore, neither patient nor investigator will know the allocated study treatment. For further details please refer to [Section 7.3.2](#).

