## 6 STUDY PROCEDURES AND VISITS / PARTICIPANT RECRUITMENT PROCESS

### 6.1 RECRUITMENT SETTING

The STROACT study will involve patients admitted to the hospital (neurological emergency unit) under emergency conditions (suspected AIS). All patients enrolled in the clinical trial, whether allocated to sequential treatment with NOAC-specific reversal agent + rt-PA or placebo control, must be managed according to local acute stroke care protocols, in the same clinical environment. Such protocols are not specified by the CTP but must follow up-to-date clinical guidelines referring to effective stroke unit care.

All clinical centres participating in the STROACT study should have an effective stroke care unit and trained personnel to provide high quality, standardised specialty care for patients with acute stroke. It includes, but is not limited to:

- Written protocol/procedures for expedite diagnosis and treatment of patients with suspected acute stroke
- Immediate access to CT or MR brain scanning (24 hours a day)
- Immediate access to laboratory (24 hours a day)
- Specialised facility where thrombolysis may be administered, and the patient monitored according to study protocol (preferably an acute stroke unit).

As a standard procedure after admission, intravenous access, monitoring of physiological variables, correction of any abnormalities, and where clinically appropriate, intravenous fluid therapy should be initiated.

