### 7.3.2 BLINDING

This study is designed as double-blind clinical trial. Once the patient has been finally qualified to receive study treatment the unblinded personnel will prepare both components of the sequential treatment. The treating physician will receive ready to use syringes for administration to the patient, which will look the same for the active treatment and placebo.

Labelling of syringes will allow for determination of antidote and IVT components to reassure correct sequential intravenous administration while maintaining double blind of study treatment.

For further details please refer to Hospital Pharmacy Manual.

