### 9.2.5 CLINICAL SAFETY LABORATORY ASSESSMENTS

**Table 4** Clinical laboratory assessments.

| Haematology/Haemostasis (whole blood)                                                                                                                                                                            | Clinical Chemistry (serum or plasma)                                                                                         |
|------------------------------------------------------------------------------------------------------------------------------------------------------------------------------------------------------------------|------------------------------------------------------------------------------------------------------------------------------|
| Haematology: CBC (including platelets count)                                                                                                                                                                     | Electrolytes (Na, K, Cl)
Blood glucose                                                                                    |
| Haemostasis: 
 
• INR, aPTT, fibrinogen
 
• Anti-IIa activity/ dabigatran concentration for dabigatrana or anti-Xa for rivaroxaban and apixaban
 
 | Kidney function: creatinine (eGFR)
Liver tests: AsPAT, AlAT, bilirubin, albumin
Inflammation: CRP
Other: Troponin I |
|                                                                                                                                                                                                                  | Other: Plasma BNP/ NT-proBNP                                                                                                 |

a In patients on dabigatran, it is possible to enroll such a subject into the study based solely on a patient's or witness' report on the last intake of the anticoagulant ie, when it was administered within the last 24 hours preceding initiation of the study treatment. In these situations, it is obligatory to collect and store blood for post-hoc anti-IIa testing. The procedure is described in the Laboratory Manual.

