The investigator should assess the available results regarding clinically relevant abnormalities. Any clinically significant abnormal laboratory values should be repeated as clinically indicated and recorded on the eCRF. Situations in which laboratory safety results should be reported as AEs are described in [Section 9.3.1](#).

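### Nothing in the protocol keeps post-dose anti-Xa results from the blinded investigator, and in groups B and C they would usually reveal the allocation

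*Protocol*

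**What the plan says.** **The promise.** Section 4.2 states that "neither patient nor investigator will know the allocated study treatment".

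**The means.** Section 7.3.2 has unblinded personnel prepare both components and hand over "ready to use syringes for administration to the patient, which will look the same for the active treatment and placebo", labelled only so that antidote and thrombolytic can be told apart. Section 1.1.6 also makes the preparers responsible for keeping clinical staff blind. Section 7.3.3 restricts unblinding to health emergencies and requires accidental unblinding to be reported. None of these sections mentions laboratory results.

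**The samples.** Section 6.5.2 requires, for apixaban and rivaroxaban patients: "Two consecutive blood sample for anti-Xa activity for rivaroxaban or apixaban must be collected". Note i to the schedule of activities (1.3) places the second sample after the antidote bolus and adds that "the third blood sample should be collected after completion of rtPA (or corresponding placebo) administration". In group A the corresponding anti-IIa measurements are optional, and note j rules out repeat dabigatran concentrations.

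**The readers.** Table 4 in 9.2.5 includes, among the clinical safety laboratory tests, "or anti-Xa for rivaroxaban and apixaban". The text below it reads: "The investigator should assess the available results regarding clinically relevant abnormalities". Section 10.4 puts all participant data on the eCRF and has the investigator verify and sign the entries. The pre-dose anti-Xa value must be available before randomisation (6.4.3), so the investigator already holds it.

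**The expected effect.** Section 2.3.1 reports, for the andexanet bleeding cohort: "Median anti-FXa activity decreased was 92% for both apixaban and rivaroxaban patients". Section 2.1 puts the onset within two minutes of the bolus and the return of activity about two hours after the infusion ends. The comparator is 0.9% NaCl for both components (6.4.2).

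**The concern.** Look-alike syringes protect the blind only if nothing measured afterwards shows what was in them. Anti-Xa is the direct pharmacodynamic readout of andexanet. An investigator who holds the pre-dose value and then sees a post-dose value can in most cases infer the arm without opening any code.

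No decision in the protocol uses the second or third value. Under 2.1, in groups B and C the rtPA bolus is given alongside the start of the antidote infusion or immediately after it, so it does not wait for the second result. Routine sight of these values therefore serves no stated trial purpose and bypasses the control in 7.3.3.

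The outcomes at stake call for judgement: NIHSS, adverse event causality (assigned to the site principal investigator in 9.3.1) and the day-90 mRS, which is the primary endpoint. The protocol names no separate rater for NIHSS or mRS. In a non-inferiority comparison, rating that favours the active group makes a false claim more likely.

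**Working it through.** **Plan's own figure.** The point rests on no figure that the plan computes. The only computed figure used below is the group size of 46 (11.3). With 40% in both groups, a 15-point margin, one-sided alpha 0.20 and 70% power: n = 2 × 0.40 × 0.60 × (0.842 + 0.524)² / 0.15² = 39.8 per group. The Hwang-Shih-DeCani parameter is not stated. Taking it between −4 and −2, as an assumption, one interim look at half the information multiplies this by 1.006 to 1.025. Dividing by 0.9 for drop-out gives 44.5 to 45.4, so 45 to 46. The stated 46 is reproduced.

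**Do both samples fall within the reversal period?**
- Second sample: after the bolus is complete. Onset is within two minutes of the bolus (2.1).
- Third sample: after the rtPA infusion, which lasts 1 hour and starts close to the beginning of the 120-minute antidote infusion (2.1, 7.1.2). If drawn promptly, it falls while the antidote is still running, and well before activity returns about two hours after that infusion ends.

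Both samples are inside the period.

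**How far apart are the arms?** Active: post-dose = baseline × (1 − 0.92). Placebo: post-dose = baseline × (1 − f), with f from 0 to 0.20 for natural decline. The documents give no placebo figure, so that range is an assumption.

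| Baseline (ng/mL) | Active | Placebo |
|---|---|---|
| 51 | 4 | 41–51 |
| 100 | 8 | 80–100 |
| 200 | 16 | 160–200 |
| 300 | 24 | 240–300 |
| 500 | 40 | 400–500 |

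For a given baseline, the active value is 0.08/1.00 to 0.08/0.80, that is 8% to 10%, of the placebo value. Because the comparison is within one patient with a known baseline, a typical pair identifies the arm.

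**How many patients?** Two arms of 92 give 184 of 276 (67%) at the minimum size. Two arms of 100 give 200 of 300 as planned (1.1.9).

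**What could it do to the primary test?** This is an illustration only. Suppose the truth is at the margin, 25% against 40%, with 46 per group and the final threshold of p < 0.176 (11.5.2.1). Then SE = √[(0.25 × 0.75 + 0.40 × 0.60)/46] = 0.0964. The chance of declaring non-inferiority is 1 − Φ(0.931 − b/SE), where b is an assumed net rating bias towards active.
- b = 0: 0.176
- b = 3 points: 0.27
- b = 5 points: 0.34
- b = 10 points: 0.54

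The documents give no basis for any particular b. The figures show sensitivity, not an expected effect.

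**The case against.** A reader might infer that the protocol sends the post-dose results to the investigator. It does not say so. Section 6.5.2 requires the samples and the recording of sampling times, and says nothing about who receives the values or when. Table 4 lists anti-Xa once, without a visit, and the pre-dose value alone could explain that entry. The sentence on investigator review speaks of available results in general. Note h wants the first sample processed at once, whereas note i only asks for the second and third to be taken, which is compatible with storage and later assay. This stands, and it limits the point to the absence of any restriction.

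A Laboratory Manual exists and is not shown. It could mask the results. However, the protocol cites it only for enrolling dabigatran patients on reported intake. If it does mask them, 9.2.5 and 10.4 as written need to be aligned with it.

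A reader might also infer that the same team gives care and rates the day-90 mRS. The protocol does not say who rates it. The mRS form in 14.2.2 is structured with yes/no items, which narrows rater discretion without removing it. Bias in outcome rating is therefore a conditional risk.

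Finally, 92% is a median from a single-group cohort of bleeding patients, with no spread given. Some individual patients could remain ambiguous, so complete separation is not shown.

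None of this supplies the missing safeguard. Read together, 9.2.5 and 10.4 make the investigator assess laboratory results and sign for all recorded data, with no exception for values that would usually disclose the arm.

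**Conclusion.** The point holds as a gap in protection. In groups B and C the protocol mandates two measurements that would usually reveal the allocation, treats the test as ordinary safety laboratory data, and nowhere keeps the post-dose values from staff who are meant to be blind. The exposure is up to 184 of 276 patients at minimum size, or about 200 of 300 as planned. Group A is exposed only where the optional post-dose anti-IIa is done; there 2.1 cites a reduction of about 88–98% after idarucizumab.

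It would go too far to conclude that the blind is in fact broken or that the primary endpoint is biased. That would require the values to reach site staff during follow-up and those staff to rate outcomes or judge causality, and the protocol states neither. The conclusion rests on the protocol's median fall applying broadly to these patients, on little change under saline, and on no masking rule existing in a document that is not shown.

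The change is worth making before further patients are enrolled, because the safeguard is cheap and no protocol decision depends on the values being seen.

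**What to change.** State in 6.5.2, in note i of the schedule of activities and in 9.2.5 that post-dose anti-Xa results, and any post-dose anti-IIa results:
- are not reported to blinded site staff;
- are excluded from the investigator review in 9.2.5 and from the blinded eCRF view, with the sign-off in 10.4 worded to match;
- are accessible only to designated unblinded personnel and the IDMC until database lock;
- are released earlier only through the unblinding procedure in 7.3.3.

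Add a cross-reference in 7.3.2 and align the Laboratory Manual.

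The cost is a small change to the laboratory reporting route and to eCRF access rights. The unblinded personnel in the protocol are described as treatment preparers, so each site must designate who receives the results. Sampling, treatment and sample size do not change. Tests ordered under local care (9.2.6) remain outside this rule. Naming a day-90 mRS rater without access to these values would be a useful additional safeguard.
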